# Effects of yoga, aerobic, and stretching and toning exercises on cognition in adult cancer survivors: protocol of the STAY Fit pilot randomized controlled trial

**DOI:** 10.1186/s13063-020-04723-2

**Published:** 2020-09-15

**Keywords:** Yoga, Cognition, Fitness, Quality of life, Executive function

## Abstract

**Background:**

Cancer survivors experience compromised quality of life due to impaired cognitive function as a result of cancer diagnosis and treatment. Although exercise has proven to be effective in improving cognitive function across the lifespan, interventions comprehensively testing the effectiveness for cancer survivors are limited. The STAY Fit Trial is a three-armed pilot randomized controlled trial designed to compare the effects of a 12-week yoga, aerobic walking, and stretch and tone intervention on cognitive function among adult cancer survivors.

**Methods:**

This pilot study aims to recruit 75 adult cancer survivors who will complete assessments of cognitive function, cardiovascular fitness, physical activity, and psychosocial measures at baseline and after the 12-week intervention. The aims of STAY Fit are (1) to assess the efficacy of yoga to improve cognitive function among cancer survivors, compared to aerobic exercise and an active control group; (2) to examine changes in cardiovascular fitness as a result of the interventions; and (3) to assess changes in quality of life among our population as a result of the exercise interventions.

**Discussion:**

The STAY Fit Trial will test the effectiveness of yoga, aerobic exercise, and stretching and toning exercises in improving cognitive function and fitness among adult cancer survivors. The results of this pilot study will enable us to understand the most effective physical activity modality to improve cognitive function in this population and potentially combat cancer-related cognitive impairment.

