### Sample size calculation

We recognize that pilot studies do not typically report formal sample size calculations. However, to aid us in making advertising and recruitment decisions, we ran a very preliminary sample size analysis to get an estimated range of subjects needed. A meta-analysis of yoga effects on cognition [13] indicated an effect size range of .32–.47 (Hedge’s g) favoring the yoga condition. We based our sample size calculations to adequately power for a small effect within this range. Using an alpha of 0.05/2, a power of 0.80, and a conservative estimate of a medium effect size (*f* = 0.35), the desired total sample size is 75 (*N* = 25 per group) for this trial.

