### Statistical analysis

Data will be analyzed using SPSS 24.0 (IBM Corp., Armonk, NY). Each of the cognitive domains assessed will be analyzed separately. From each of the assessments administered, latent variables will be created to represent a global cognitive score for each domain. These variables will be created for both baseline and post-intervention test scores. Given the pilot nature of this study, we will focus on descriptive statistics and calculating effect sizes (Cohen’s d values). Data characteristics permitting (normality, multi-collinearity, sample size), we may conduct additional secondary analyses. For example, a time (baseline, follow up) × group (yoga, aerobic, stretching-toning) repeated measures analyses of covariance controlling for relevant covariates (possible covariates include age, education, stage of cancer, months since diagnosis, attendance, and baseline performance) can be employed to explore intervention effects for each of the cognitive domains. Similar repeated measures analyses could examine intervention effects for cardiovascular fitness and the tertiary psychosocial outcomes. Given that this is a pilot study, no additional subgroup or adjusted analyses are planned. An intent-to-treat analysis approach will be used for any dropouts who completed at least one exercise session. Missing data will be handled using a mean imputation approach. Participants’ exercise session attendance and physical activity performed outside of the session (as reported in home logs) will be factored into analyses as appropriate to control for participants’ adherence to study protocols.

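### The article promises to show which exercise modality is most effective, but its committed analysis is descriptive and 25 per arm cannot establish a ranking

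*Protocol article*

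**What the plan says.** The Discussion part of the abstract says that the results of the pilot will "enable us to understand the most effective physical activity modality to improve cognitive function in this population". The Conclusions section adds, also without a hedge, that the study will establish whether yoga is efficacious for cognitive health.

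The Statistical analysis section commits to less: "Given the pilot nature of this study, we will focus on descriptive statistics and calculating effect sizes (Cohen’s d values". Inferential work is conditional: "Data characteristics permitting (normality, multi-collinearity, sample size), we may conduct additional secondary analyses". The example given is a time × group repeated measures model that "can be employed to explore intervention effects for each of the cognitive domains". On the several outcomes it says "Each of the cognitive domains assessed will be analyzed separately", and it gives no way of combining them.

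The Background describes a trial meant to test feasibility and explore possible effects. The Discussion section hopes to inform a later, fully powered efficacy trial. The Sample size calculation section cites a meta-analysis that "indicated an effect size range of .32–.47 (Hedge’s g) favoring the yoga condition" and arrives at 25 participants per arm.

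**The concern.** Saying which of three programmes is most effective is a ranking claim. It needs between-arm comparisons with a measure of uncertainty, and it must be possible to conclude that no arm was shown to be better. The committed analysis produces point estimates. Sorted by size, point estimates always have a first place, whether or not the programmes differ.

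What is at stake is what the trial may conclude. The pilot is meant to inform a larger trial, and the Conclusions section speaks of recommendations for cancer survivors. If the order of three small-sample effect sizes is reported under the abstract's heading of most effective, readers may take chance variation for a finding.

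**Working it through.** **1. The plan's own figure.** Inputs from Sample size calculation: "Using an alpha of 0.05/2, a power of 0.80", f = 0.35, three groups, total 75. The article does not name the test or a correlation. A noncentral F calculation for the between-groups factor of a repeated measures ANOVA (3 groups, 2 time points, assumed correlation 0.5) has noncentrality f²·N·m/(1 + (m−1)ρ) = 0.1225 × 75 × 2/1.5 = 12.25 on 2 and 72 degrees of freedom. The smallest N giving 80% power is 75, so the figure reproduces under that assumption. A one-way three-group ANOVA at alpha 0.025 would need 98. In two-group terms f = 0.35 is d = 2 × 0.35 = 0.70, well above the cited 0.32–0.47. The stated sample size therefore does not give power for ranking arms that differ by the cited amount.

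**2. Precision of one between-arm d.** With 25 per arm, SE(d) = √(2/25 + d²/100).
- d = 0: √0.08 = 0.283; half-width 1.96 × 0.283 = 0.55.
- d = 0.32: 95% interval −0.24 to 0.88.
- d = 0.47: 95% interval −0.09 to 1.03.

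Baseline adjustment multiplies the half-width by about √(1 − r²): 0.55 × 0.866 = 0.48 at an assumed r = 0.5, and 0.55 × 0.714 = 0.39 at r = 0.7. Two-sided pairwise power without adjustment is 20% at d = 0.32 and 38% at d = 0.47 (alpha 0.05), or 13% and 28% (alpha 0.025).

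**3. Gap between the best and worst arm when all three are equal.** Each arm mean has standard error √(1 − r²)/√25 in SD units. Results of 200,000 simulated trials:

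| Baseline correlation r | Mean gap | P(gap ≥ 0.32) | P(gap ≥ 0.47) |
|---|---|---|---|
| 0 (no adjustment) | 0.34 | 49% | 22% |
| 0.5 (assumed) | 0.29 | 39% | 13% |
| 0.7 (assumed) | 0.24 | 25% | 5% |

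**4. Which arm comes first when one is truly better.** Without adjustment, an arm better than both others by 0.32 ranks first in 79% of trials (92% at 0.47). If the second arm has half that benefit (assumed), the figures are 66% and 78%. At r = 0.7 with the half-benefit assumption they are 76% and 87%. The order carries some information, but the order alone does not show whether a given lead is real.

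**5. Several domains.** The Background lists five cognitive domains and the Measures section groups them as four. With equal arms and independent domains, the chance that one arm leads in all of them is 3 × (1/3)⁴ = 4% for four and 3 × (1/3)⁵ = 1% for five. At an assumed between-domain correlation of 0.3 it is 14% and 9%; at 0.5 it is 25% and 19%. In most such trials the domains would have different leaders.

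All of this takes 25 analysed per arm. No dropout allowance is stated, so this is the best case.

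**The case against.** The strongest reply is that the trial never says it will crown a winner. That is correct. A reader might infer a rule under which the arm with the largest d is declared best, so that the trial names a winner every time. The documents do not support this. No section states such a rule. The Conclusions allow for yoga being merely as good as aerobic exercise, and the optional time × group model could show no difference. Some arm always comes first only within a single domain, and no overall winner follows when domains are analysed separately.

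A reader might also infer that a chance leader will decide which modality goes into the larger trial. No go-forward or arm-dropping criterion is written, so that too goes beyond the text.

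The article is condensed, and intervals or contrasts may be specified in a fuller plan. Their absence is therefore not the finding. Nor does the article say whether d compares arms or measures pre–post change; the working above takes the between-arm reading. The size of the problem also depends on baseline adjustment: at r = 0.7 the average chance gap of 0.24 falls below the cited range.

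The last defence is that this is openly a pilot, and the abstract's own sentence says so. That does not remove the point. The pilot framing in the Background and Discussion conflicts with an unhedged promise to learn which modality is most effective; it does not qualify that promise.

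**Conclusion.** The point stands as a mismatch between stated conclusions and committed analysis. The abstract and the Conclusions promise a ranking and an efficacy answer. The article commits only to descriptive effect sizes, and 25 per arm cannot carry more. A between-arm d has a 95% half-width of about 0.55 unadjusted, or 0.39–0.48 with adjustment at assumed correlations of 0.7 and 0.5, against a cited effect of 0.32–0.47. Equal programmes would show a best-to-worst gap of 0.32 or more in 25% to 49% of trials, depending on the baseline correlation, which the article does not give. The correction concerns wording and reporting; the design need not change.

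**What to change.** In the abstract, replace the ranking sentence with: *The trial will estimate pairwise differences between modalities in cognitive change, to inform a larger trial.* Bring the efficacy sentence in the Conclusions into line with it.

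In Statistical analysis, commit to reporting the three baseline-adjusted pairwise standardised differences for each domain with 95% confidence intervals. State that no modality will be called most effective from the order of point estimates alone.

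A formal rule that a winner must beat both other arms under Tukey's procedure is not required. It would name an arm in 0.4% of trials with no difference, but in only 3.8% when one arm is truly better by 0.32 and 11.7% at 0.47, which is debatable for a pilot.

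The cost is small: three intervals per domain, 12 to 15 in all for four or five domains. The pilot will usually have to report that no ranking was established.

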**Trial registration:**

ClinicalTrials.gov NCT03650322. Registered on 28 August 2018.

## Background

Cancer is among the leading causes of death worldwide, yet scientific advances in prevention, diagnosis, and treatment have led to an increased number of cancer survivors estimated to be almost 19 million by 2024 [1]. However, survivorship does not come without an aftermath of physical health and quality of life complications. In 1998, the President’s Cancer Panel and the National Coalition for Cancer Survivorship formally recognized cancer-related cognitive impairment (CRCI) as a quality of life matter that deserved higher priority in clinical research [2]. CRCI is the loss of mental acuity associated with cancer and cancer treatment. About 75% of all cancer survivors report poorer attention and memory following treatment and the clinical prevalence of treatment-related cognitive impairment ranges from 17 to 75% [3, 4]. Cognitive processes thought to be impacted include impairment of memory, learning, concentration, reasoning, executive function, attention, and visual-spatial skills [5]. Despite the prevalence of cognitive impairment in cancer survivors, it is largely underdiagnosed and often left untreated [5, 6].

Although research on the beneficial effects of exercise training on cognitive functioning in non-clinical populations continues to emerge, parallel research examining cognitive functioning in cancer survivors is lagging. Among cancer survivors, many age-related physical and functional declines can be mitigated with exercise training [7]. In intervention studies, regardless of intervention specifics, exercise has been shown to improve quality of life and psychosocial and physical health outcomes in various cancer survivor groups during and after cancer treatment and may also help to manage long-term effects of treatment [8]. A majority of these interventions test aerobic exercise modalities, such as walking, as it is associated with improved health and cognitive function [9, 10]. However, few studies have examined the health benefits of yoga practice on cancer patients [11] and survivors [12].

Yoga is a noteworthy exercise modality that should be examined for its improvements in cognitive function and quality of life in clinical populations. As a holistic, mind-body activity, with components centered on meditation, breathing, and postures, it has shown great potential to improve cognitive function [13, 14]. Moreover, it is a low-impact exercise modality that may be more suitable by people limited in their mobility and function. However, little is known about the potential of yoga in maintaining or enhancing cognitive function and/or reducing CRCI among cancer survivors. An evidence-based review of yoga for cancer patients and survivors [15] reviewed 10 yoga-based interventions and noted some positive results, with outcomes primarily focused on psychosocial health and well-being (quality of life, depression, anxiety and stress being the most common). None of the reviewed interventions addressed cognitive function or CRCI.

STAY Fit is designed as a pilot three-arm randomized controlled trial, comparing the benefits of a 12-week yoga and aerobic walking intervention, using a stretching-toning group as an active control. In line with the purpose of conducting pilot studies, we designed this trial to test the feasibility of our methods and procedures for a future large-scale intervention and to explore possible effects and associations as a function of yoga practice on cognitive health [16]. The primary outcomes are measures of cognitive function, specifically domains of executive function, attention, memory, processing speed, and working memory. Secondary outcomes include cardiovascular fitness changes over the course of the intervention. Tertiary measures will examine changes in self-reported quality of life and psychosocial outcomes. Our protocol has been reported here in accordance with the SPIRIT checklist (see Additional file 1).

## Methods

### Study design

The STAY Fit trial is a three-arm randomized clinical exercise trial comparing the effects of a 12-week group-based yoga exercise, aerobic walking, and an active control (stretching and toning) on cognitive function and cardiovascular fitness among adult cancer survivors. We will randomize 75 low active adults between the ages of 30 and 70 years to one of the three conditions. All groups participate in structured group-based exercise led by certified and trained exercise leaders over the course of the 12-week intervention. Study outcomes include cognitive assessments, cardiovascular fitness, and psychosocial questionnaires administered at baseline and following the 12-week intervention.

### Duration of study

August 2018–May 2020.

### Subjects

The inclusion criteria are low physical activity engagement (i.e., less than 150 min of moderate to vigorous exercise per week), including no yoga practice over the last 6 months; aged between 30 and 70 years; capable of performing yoga, aerobic walking, or stretching and toning exercise without any pre-existing condition(s), as determined by their personal physician; the type of cancer (i.e., types of brain cancers are excluded as they could confound with cognitive study outcomes); the last treatment for cancer being at least 1 year from the beginning of the exercise program; not planning to receive any cancer-related treatment during the study period; intention to stay in the Champaign-Urbana area over the duration of the study; comfortable with reading, writing, and speaking English; and willingness to be randomized. Finally, all participants will be required to complete the Physical Activity Readiness Questionnaire (PAR-Q [17];) and must obtain approval from their personal physician, if deemed high-risk on the PAR-Q. The physician approval process will be facilitated by the research staff to minimize participant burden.

### Recruitment procedures

Our recruitment efforts include print, audio, and online media outlets to publicize the STAY Fit study in the Champaign-Urbana communities. All advertising materials include the key characteristics of the study—a free 12-week exercise program, opportunity to meet other cancer survivors from the community, monetary compensation for participation, and free parking. We will advertise in the local newspaper and place short ads on local radio, as well as attend various cancer survivorship and awareness events in the local area to distribute flyers and brochures to the attendees. Additionally, we will attend events at the local libraries and churches to distribute brochures. Finally, we will send an email or a letter to participants in the lab database who have been ineligible for previous studies with an invitation to participate in the new STAY Fit study (if deemed eligible). A schedule of enrollment, interventions, and assessments is presented in Fig. 1.

**Fig. 1 Fig1:**
[figure not shown]
The STAY Fit Trial schedule of enrollment, interventions, and assessments

All participants who express interest will be provided with a description of the study and screened for eligibility. All participants will be required to read and sign a University Institutional Review Board-approved informed consent prior to study participation and data collection. Upon enrollment in the study, each participant will be assigned a random unique identification (ID) number as the only way to match collected data to their identifiable information. An electronic database, stored on a secure password-protected network only accessible by the study investigators, will house the key linking participant information and ID number. All written hard copies of participant data collected during the study period will only have the ID number written on them and will be stored in a secure location on the research site. Upon completion of the study, the key linking ID numbers and participant information will be destroyed. Participants will be informed that their de-identified data may be made available to regulatory authorities or ancillary individuals from the university, upon reasonable request. A snapshot of the flow of participants through the STAY Fit study is presented in Fig. 2.

**Fig. 2 Fig2:**
[figure not shown]
Flow of participants through the STAY Fit Trial

### Randomization

Participants who are eligible for the study and complete all baseline measurements will be randomly assigned to 1 of the 3 intervention arms using a computer-generated program. Randomization will take place in groups following rounds of advertising and is stratified based on sex, age, and years since cancer diagnosis. Couples or friends who sign up for the study together will be randomized together to avoid contamination across groups. Randomization will take place following completion of all baseline assessments and a week before the 12-week exercise sessions are scheduled to begin. Participants will be notified via a mailed letter and follow-up phone calls confirming their randomized group and logistics (parking and directions) for their 12-week exercise sessions. This is an open label trial with no blinding of participants or assessors.

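### Stratifying individuals while keeping couples and friends in one arm gives two rules that clash for mixed pairs; no precedence is stated, and baseline cognition is left out of allocation and firm adjustment

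*Protocol article*

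**What the plan says.** The Randomization section of the protocol article sets out four things.

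- Timing and tool: "Participants who are eligible for the study and complete all baseline measurements will be randomly assigned to 1 of the 3 intervention arms", by a computer program. The section repeats that this follows completion of all baseline assessments, a week before sessions start.
- Batches and strata: "Randomization will take place in groups following rounds of advertising and is stratified based on sex, age, and years since cancer diagnosis".
- Pairs: "Couples or friends who sign up for the study together will be randomized together to avoid contamination across groups".
- Blinding: none, for participants or assessors.

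The article gives no cut-points for age or years since diagnosis, no number of rounds, no block size or other restriction, and no rule for a pair whose members belong to different strata. It does not call round a stratum and does not say that lists restart each round. Under Subjects, eligible participants are "aged between 30 and 70 years".

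Under Sample size calculation, "the desired total sample size is 75 (*N* = 25 per group) for this trial".

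Under Statistical analysis, the committed output is descriptive statistics and Cohen's d. A repeated measures analysis of covariance may be added if the data permit. Its possible covariates include age, months since diagnosis and baseline performance; sex is not on the list. No further adjusted analyses are planned.

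**The concern.** Two adjacent sentences set rules that cannot both hold for some of the people they cover. Stratification assigns each individual from the list of his or her own stratum; the pair rule assigns two individuals one arm. When the members sit in different strata, one list must be overridden. Without a written precedence, that override is left to staff in an open-label trial, and the second member is placed without regard to the balance of his or her own stratum.

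Two further matters bear on how well the scheme balances the arms. Three stratifiers and three arms spread 75 people thinly. And the baseline cognitive score, likely to be a strong predictor of the primary outcome and already measured when each batch is allocated, is used neither in allocation nor with certainty in the analysis. At stake is comparability of the arms on the variables the design itself names, and on cognition.

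**Working it through.** **The plan's own figure.** The inputs are three groups, "Using an alpha of 0.05/2, a power of 0.80" and f = 0.35. A one-way ANOVA at alpha 0.025 needs 98. A between-groups effect in a repeated measures ANOVA with two measurements and correlation 0.5 (assumed; not stated) has noncentrality f² × N × 2/(1 + 0.5) = 0.1225 × 75 × 1.333 = 12.25. It gives power 0.806 at N = 75 and 0.799 at N = 74. So 75 is reproducible, and it is not disputed here. It implies 25 per arm.

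**The conflict.** A man and a woman enrolling together are in different sex strata with certainty. If each is drawn from an independent, equally weighted three-arm list, both get the same arm with probability 3 × (1/3)² = 1/3. About 2/3 of such couples would need one list overridden. Friends who differ in age band or years since diagnosis meet the same problem.

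**How many pairs straddle strata.** The documents give no pair frequency. Assume a 75/25 sex split, two-level age and years since diagnosis at 50/50, and independent members. Two people then share a stratum with probability (0.75² + 0.25²) × 0.5 × 0.5 = 0.156, so 84% straddle. If friends are of the same sex and age band, only 50% do. The share depends on how alike pairs are.

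**People per cell.** Mean = 75/(strata × rounds). Levels and rounds are assumptions; the first column applies when lists run on across rounds.

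| Strata | Carried over | 2 rounds, restarted | 3 | 4 | 5 |
|---|---|---|---|---|---|
| 8 (2×2×2) | 9.4 | 4.7 | 3.1 | 2.3 | 1.9 |
| 12 (2×3×2) | 6.3 | 3.1 | 2.1 | 1.6 | 1.3 |
| 18 (2×3×3) | 4.2 | 2.1 | 1.4 | 1.0 | 0.8 |

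**Arm sizes.** Simulation with 1,500 runs per setting, 8 strata, 75% in one sex (assumed), and each pair allocated from one member's stratum. The range runs from the 5th percentile of the smallest arm to the 95th percentile of the largest.

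| Scheme | Range | Exactly 25/25/25 |
|---|---|---|
| Blocks of 3, carried over, no pairs | 23–27 | 15% |
| Blocks of 3, carried over, 10 pairs | 21–29 | 5% |
| Blocks of 3, restarted over 4 rounds, 10 pairs | 19–31 | 2% |
| Blocks of 6, restarted over 4 rounds, 10 pairs | 18–32 | 1% |

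**Precision cost.** The ratio of standard errors is √[(1/a + 1/b)/(2/25)].

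- 20 versus 30: √(0.08333/0.08) = 1.021.
- 18 versus 32: √(0.08681/0.08) = 1.042.

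**Baseline cognition.** For two arms of 25, the standard error of the difference in means is √(2/25) = 0.283 SD. Then P(|difference| > 0.3 SD) = 2 × [1 − Φ(0.3/0.283)] = 2 × [1 − Φ(1.06)] = 0.29. The probability that at least one of the three arm pairs differs by that much is 0.54. For scale, the effect range cited in the sample size section starts at 0.32.

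**What such a gap does to an unadjusted comparison.** Take equal variances and a baseline to follow-up correlation r (assumed 0.5 or 0.7). A 0.3 SD baseline gap shifts the expected post-score difference by r × 0.3 = 0.15 or 0.21 SD. It shifts the change-score difference by −(1 − r) × 0.3 = −0.15 or −0.09 SD. Baseline-adjusted analysis removes both.

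**The case against.** The strongest reply is that a journal article commonly leaves cut-points, block size and pair handling to the full protocol. The article names no blocks and no lists, only a computer program applied to a known batch; that is compatible with allocating pairs as units in a balanced way. Drawing the pair from one member's stratum would also resolve the clash. Much of this stands: missing cut-points and block sizes are not held against the plan. What remains is that two stated rules conflict, with nothing to say which gives way.

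Three stronger readings are tempting and are not supported.

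- A reader might infer that cells hold only 2–3 people. With 8 strata that needs lists restarted in each of 3–4 rounds. The article neither gives the number of rounds nor makes round a stratum; carried over, the average is 9.4.
- A reader might infer that 25 per arm will not be delivered, with serious loss. Equality is not assured, but under blocked allocation the loss of precision is about 2–4%. The article calls its sample size analysis very preliminary and 75 a desired total.
- A reader might blame the pair or stratum rules for imbalance in baseline cognition. The 29% is ordinary chance imbalance with equal arms of 25 on any variable that is not balanced.

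It is also fair to say that the article does not fix whether Cohen's d uses post-scores or change, so a baseline gap need not pass straight into it. Either way part of the gap remains unless baseline is adjusted for.

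**Conclusion.** The point holds in a limited form. Individual stratification and the shared-arm rule cannot both be followed under separate stratum lists when a pair's members are in different strata, which is certain for opposite-sex couples, and no precedence is stated. With at least 8 strata (two levels per factor, the minimum) cells average about 9 or fewer, so stratified balance and exactly 25 per arm are not assured. The efficiency cost of unequal arms is small, about 2–4% on the standard error in the more unequal splits considered.

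Separately, two arms of 25 have a 29% chance of differing by more than 0.3 SD at baseline on cognition. Leaving that score out of allocation is not an error. But it is available at the time, adjustment for it is only a possibility, and sex, a stratifier, is not among the listed covariates. Using these variables in both places is a real gain at little cost. The number of rounds, factor levels, share of pairs and block scheme are all assumptions; the existence of the conflict depends only on separate stratum lists.

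**What to change.** Allocate each completed batch by minimisation or constrained randomisation that keeps a random element.

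- Make the couple or friend group the unit allocated, and single participants units of one.
- Balance arm size, sex, age, years since diagnosis and a simple baseline cognitive composite marginally rather than in cross-classified cells, cumulatively over rounds.
- Compute the reported effect sizes from a model adjusted for the baseline score and these allocation variables, in place of an unadjusted Cohen's d with optional adjustment.

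In a small simulation (100 runs, 20% of participants in pairs and 3 or 5 rounds assumed), constrained allocation gave an average gap between largest and smallest arm of 1.9 or 1.5. A baseline cognition gap above 0.3 SD between two given arms occurred in about 1% of runs or fewer. With so few runs these figures are approximate.

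The cost is a somewhat more complex allocation program, which must be documented, and baseline tests must be scored before each batch is allocated. No extra participants or visits are needed. If the stratified scheme is kept, the minimum is to state how a pair in different strata is allocated and whether lists carry over between rounds.
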